### **Re-induction:**

Patients who progress following stable disease of  $\geq 3$  months duration starting from diagnosis at week 12 tumor assessment or patients who have progressed following an initial response (partial or complete) assessed at week 12 may be offered additional cycles of therapy with the originally assigned treatment regimen until off-treatment criteria are met, provided they meet re-treatment eligibility requirements. Please note that re-induction is allowed only if progressive disease was confirmed within not less than 4 weeks. No patient will be re-treated if they experience a Grade 3 or higher gastrointestinal or certain other immune-related adverse events (irAE) (refer to section 5.2 and 5.3). No patient with disease progression following the first cycle of study medication will be permitted to be re-treated with study medication.

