## 5.2 Re-Induction Treatment

Patients who have progressed following stable disease (SD) of  $\geq 3$  months duration from Week 12 assessment OR patients who have progressed following an initial response to the induction treatment (CR or PR diagnosed at week 12 assessment) may be offered additional cycles of therapy (4 infusions of ipilimumab 3mg/kg every 3 weeks) with the originally assigned treatment regimen ("Re-induction") until off-treatment criteria are met, provided they meet re-treatment criteria specified below.

- Re-treatment criteria:

Patients who received ipilimumab as induction in this study and have met each of the following criteria within **28 days** before re-treatment, are eligible for "re-induction":

- Had no unacceptable toxicity requiring ipilimumab discontinuation; OR
  - Patients who did not permanently discontinue treatment due to select irAEs as follows:
    - Reversible autoimmune hepatitis
    - Medically manageable endocrinopathy
    - Reversible dermatological toxicity
  - ECOG performance status of 0, 1 or 2
  - Electrocardiogram (ECG): during screening and week 12. Patients with an existing myocarditis are excluded from this study. For patients with suspicion of myocarditis e.g. dyspnoea, functional insufficiency etc. ECG examinations have to be performed before each treatment.
  - Patient must meet all other inclusion criteria as outlined before (see Inclusion criteria)
- AND
- Have experienced disease progression as documented by physical examination or diagnostic imaging (including brain imaging) after demonstrating expanded clinical benefit (see below).

All patients eligible for Re-induction treatment with ipilimumab their TSH level must be assessed at baseline and before each dose and the TSH level be available to the investigator prior to the administration of the dose. **The assessment of TSH is mandatory prior each treatment.** If a subject has thyroid dysfunction and concomitant symptoms (i.e. fatigue), the subject should be monitored more frequently and be treated as per standard medical practice.

The management algorithm for endocrine abnormalities is available on page 59 (appendix 10-15).

- Re-induction treatment:

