During the Re-Induction treatment, subjects enrolled who are eligible for additional treatment cycles will repeat the treatment phase as outlined in INDUCTION TREATMENT. They will receive ipilimumab at the 3 mg/kg dose level every 3 weeks for the first 10 weeks (Weeks 1, 4, 7 and 10) of Re-induction.

Ipilimumab therapy should be offered to all subjects who have not experienced unacceptable toxicity (refractory Grade > 3 irAEs) and are considered by the investigator to be obtaining clinical benefit, either because of apparent tumor stability or continued shrinkage and/or late response. No patient will be re-treated if they experience a Grade 3 or higher nondermatologic autoimmune breakthrough event (ABE) considered related to study therapy or a Grade 3 or higher gastrointestinal or certain other immune-related adverse events (irAE) which require permanent discontinuation of ipilimumab (refer to section 5.5.3). If a patient has experienced a study medication-related dermatologic or non-dermatologic ABE < Grade 3, then the event must have improved to Grade 1 or less before re-treatment can be considered. No patient with disease progression following the first cycle of study medication will be permitted to be re-treated with study medication.

Patients can be eligible for more than one re-induction. The number of re-inductions is not limited. All re-inductions initiated while patient is on-study (**each patient study period**, first dosing + 12 months) will be performed in the frame of the study. Any re-induction starting after each patient study period (first dosing + 12 months) would be done outside of the study.

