### 5.3 Definition of Selected Reversible irAEs that May be Considered For Re-Treatment

Patients with selected irAEs related to ipilimumab that have completely resolved with immunosuppressive therapy or are adequately controlled with hormone therapy, may be considered for further re-treatment with ipilimumab under this study, at the time of disease progression. The list of completely reversible or medically managed immune-related adverse events (irAEs) eligible for consideration is:

- Reversible autoimmune hepatitis
- Medically managed endocrinopathy
- Reversible dermatological toxicity

All other irAEs are not considered eligible for re-treatment, including, but not limited to,

≥ Grade 3 colitis or diarrhea, or uveitis of any grade.

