#### **5.5.4 Immune-Related Adverse Events (irAEs): Definition, Monitoring, and Treatment**

Blocking CTLA-4 function may permit the emergence of auto-reactive T cells and resultant clinical autoimmunity. Rash/vitiligo, diarrhea/colitis, uveitis/episcleritis, hepatitis, and hypopituitarism were drug-related, presumptive autoimmune events, now termed irAEs, noted in previous ipilimumab studies.

For the purposes of this study, an irAE is defined as an AE of unknown etiology associated with drug exposure and consistent with an immune phenomenon. Efforts should be made to rule out neoplastic, infectious, metabolic, toxin or other etiologic causes prior to labeling an AE an irAE. Serological, immunological, and histological (biopsy) data should be used to support

the diagnosis of an immune-mediated toxicity. Suspected irAEs must be documented on an AE or SAE form.

Patients should be informed of and carefully monitored for evidence of clinically significant systemic irAE (e.g., systemic lupus erythematosus-like diseases) or organ-specific irAE (e.g., rash, colitis, uveitis, hepatitis or thyroid disease). If an irAE is noted, appropriate work-up (including biopsy if possible) should be performed, and steroid therapy may be considered if clinically necessary.

It is unknown if systemic corticosteroid therapy has an attenuating effect on ipilimumab activity. However, clinical anti-tumor responses have been maintained in patients treated with corticosteroids and discontinued from ipilimumab. If utilized, corticosteroid therapy should be individualized for each patient. Prior experience suggests that colitis manifested as  $\geq$  Grade 3 diarrhea requires corticosteroid treatment.

Specific treatment algorithms for immune-related adverse events are included as appendices in the IB.

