**Appendix 7: Patient Information and Informed Consent**

## Appendix 8: irAE Treatment Algorithm

### Re-Induction:

Patients who progress following stable disease of  $\geq 3$  months starting from diagnosis at week 12 tumor assessment duration from beginning of induction treatment or or patients who have progressed following an initial response (partial or complete) assessed at week 12 may be offered additional cycles of therapy with the originally assigned treatment regimen until off-treatment criteria are met, provided they meet re-treatment eligibility requirements. Please note that progressive disease must be confirmed within not less than 4 weeks.

Re-induction is not allowed in patients who experience

- At least one Grade 3 or higher gastrointestinal immune-related adverse events (irAE) including, but not limited to,  $\geq$  Grade 3 colitis or diarrhea **OR**
- Uveitis of any grade **OR**
- At least one certain other immune-related adverse events (irAE) (refer to section 5.2 and 5.3) **OR**
- Disease progression following the first cycle of study medication

Exemption: Re-induction is allowed in patients who experience selected irAEs related to ipilimumab that have completely resolved with immunosuppressive therapy or are adequately controlled with hormone therapy, may be considered for further re-treatment with ipilimumab under this study, at the time of disease progression. The list of completely reversible or medically managed immune-related adverse events (irAEs) **eligible** for consideration is:

- Reversible autoimmune hepatitis
- Medically managed endocrinopathy
- Reversible dermatological toxicity

All other irAEs are not considered eligible for re-treatment!

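### Sections 5.2 and 5.3/Appendix 8 give different answers on re-induction after a cleared gastrointestinal irAE of Grade 1-2

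*Protocol*

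**What the plan says.** **Texts that start the bar at Grade 3 or at discontinuation**

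- Protocol 5.2, first re-treatment criterion: "Had no unacceptable toxicity requiring ipilimumab discontinuation; OR". The three-item list (hepatitis, endocrinopathy, dermatological toxicity) follows as the alternative branch.
- Protocol 5.2, re-induction treatment: re-treatment is refused after related non-dermatologic breakthrough events, or gastrointestinal and certain other irAEs, from Grade 3 upward. For a related event below that: "dermatologic or non-dermatologic ABE < Grade 3, then the event must have improved to Grade 1 or less before re-treatment can be considered".
- Synopsis, Re-induction: "No patient will be re-treated if they experience a Grade 3 or higher gastrointestinal or certain other immune-related adverse events (irAE".
- Sections 1.2 and 1.5: patients who benefited and had no irAE of Grade 3 or above qualify.
- Appendix 8, first bar: "At least one Grade 3 or higher gastrointestinal immune-related adverse events (irAE".

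**Texts with no grade limit**

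- Protocol 5.3, after the three-item list: "All other irAEs are not considered eligible for re-treatment, including, but not limited to". The examples that follow are colitis or diarrhoea from Grade 3 upward, and uveitis: "Grade 3 colitis or diarrhea, or uveitis of any grade".
- Appendix 8, last line, with no examples: "All other irAEs are not considered eligible for re-treatment".

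**The concern.** Re-induction is part of the study treatment as the synopsis defines it, and up to 26 sites apply the rule. Gastrointestinal irAEs are not among the three permitted types. For a patient with a cleared Grade 1-2 event, a site working from 5.2 may offer four more infusions, while a site working from the last line of 5.3 or Appendix 8 must refuse.

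Both errors have a cost. Section 1.3.5.a names gastrointestinal perforation as the most common cause of drug-related death, so re-exposure after a bowel event needs a clear rule. A wrong refusal withholds treatment from a patient who benefited from induction. The number of re-inductions is not limited, so the question can recur in the same patient.

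**Working it through.** **1. One test patient under each text.** The patient had related Grade 2 diarrhoea during induction, it cleared, ipilimumab was not permanently stopped, and the disease progressed after a Week 12 response.

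- 5.2, first criterion: met, because no toxicity required discontinuation. Under 5.5.2 a related Grade 2 non-skin event may lead to a skipped dose. The gastrointestinal guidance in Appendix 10-15 requires a skip at Grade 2 and recommends permanent discontinuation from Grade 3.
- 5.2, rule below Grade 3: met, because the event is at Grade 1 or less.
- Synopsis, 1.2, 1.5 and the first bar of Appendix 8: not barred, because the event stayed below Grade 3.
- 5.3, closing sentence: barred, because diarrhoea is not one of the three types and the sentence sets no grade.
- Appendix 8, last line: barred for the same reason.

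The patient is admitted by one set and excluded by the other. No sentence ranks them.

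**2. Are ABE and irAE the same class?** 5.2 uses both terms. Section 5.5.4 describes "presumptive autoimmune events, now termed irAEs" and includes diarrhoea/colitis among them. Treating the terms as equivalent is an inference, but the conflict does not depend on it: the first criterion of 5.2 speaks of toxicity, and the synopsis, 1.2, 1.5 and Appendix 8 speak of irAEs.

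**3. Frequency at 3 mg/kg.** Inputs are from the CA184-022 table in 1.3.5.b (n = 71).

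- Any gastrointestinal irAE: 32.4% × 71 = 23. Grade 3-4: 2.8% × 71 = 2.
- Grade 1-2 at most: 23 − 2 = 21, and 21/71 = 29.6%. This reproduces the 30% in 1.3.4c.
- Clopper-Pearson 95% CI: lower = Beta quantile 0.025 with parameters (21, 51) = 19.3%; upper = Beta quantile 0.975 with parameters (22, 50) = 41.6%.
- Some of the 21 may have had a different Grade 3-4 irAE. Any Grade 3-4 irAE: 7.0% × 71 = 5, of which 2 were gastrointestinal, so at most 3 of the 21. Then 18/71 = 25.4%.
- Other categories at Grade 1-2: skin (32 − 1)/71 = 43.7%, endocrine (4 − 2)/71 = 2.8%, hepatic 0. Skin, endocrine and hepatic are the permitted types, so gastrointestinal is the only category in the table outside the list.

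**4. Scale in this trial.** If the rate carried over to 200 treated patients, 0.296 × 200 = 59 would have such an event (39 to 83 by the interval). The share reaching re-induction is not in the protocol. Assuming 5% to 20%, there would be 10 to 40 candidates. Those meeting the conflict would number 0.254 × 10 = 2.5 to 0.296 × 40 = 11.8. With the interval included, the range is 0.193 × 10 = 1.9 to 0.416 × 40 = 16.6, or about 2 to 17.

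**The case against.** The best counter-reading is that context resolves the matter. The title of 5.3 concerns selected reversible irAEs, its three items repeat the alternative branch of 5.2, and Appendix 8 places the list under an exemption after stating the bars. On that view the closing line means only that no further exemptions exist, and a cleared Grade 1-2 diarrhoea needs none. The strict reading would also make the Grade 3 limit on diarrhoea and the any-grade wording for uveitis in 5.3 redundant.

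This is probably what was intended, but the text does not say it. The examples in 5.3 are expressly not exhaustive, the uveitis example shows that the sentence reaches below Grade 3, and Appendix 8 repeats the line without examples.

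A second argument is that the sentence in 5.2 on events below Grade 3 is only a necessary condition, which 5.3 may narrow. That does not reconcile the texts, because the first criterion of 5.2 and the statements in 1.2 and 1.5 still admit the patient.

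Three stronger inferences are not supported:

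- **Every unlisted irAE below Grade 3 is in conflict.** Uveitis is not; 5.3 and Appendix 8 bar it by name at any grade.
- **The survival result is compromised.** Section 9.5 measures survival and PFS regardless of re-induction, so the primary endpoint is calculated the same way under either rule.
- **A known number of patients is affected.** The share reaching re-induction is an assumption. CA184-022 also gave maintenance doses after induction, which this trial does not, and its figure covers all gastrointestinal irAEs, not diarrhoea alone.

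**Conclusion.** The inconsistency is real and limited. For a related gastrointestinal irAE that stayed at Grade 1-2, is now at Grade 1 or less and did not require discontinuation, 5.2 and the texts that agree with it permit re-induction, while the literal closing lines of 5.3 and Appendix 8 forbid it. About 30% of patients at 3 mg/kg in CA184-022 had such an event (21/71, 95% CI 19.3% to 41.6%).

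The 2 to 17 candidates rest on the assumed 5% to 20% reaching re-induction and on candidates having the same event rate as all treated patients. Section 1.3.6.a hints that the rate may be higher among patients with response or stable disease, but calls this statistically inconclusive.

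The consequence is inconsistent treatment decisions on a safety-relevant point. The definition and calculation of the primary endpoint do not change. The point merits correction because it decides who receives more drug and costs little to settle.

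**What to change.** Replace the closing line in 5.3 and in Appendix 8 with: *All other irAEs that were Grade 3 or higher, or that required permanent discontinuation under 5.5.3 at any grade, and uveitis of any grade, rule out re-treatment; other related irAEs below Grade 3 need to have returned to Grade 1 or less (see 5.2).*

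The reference to 5.5.3 is needed. Section 5.5.3.a requires permanent discontinuation for some events below Grade 3, such as Grade 2 eye pain needing systemic treatment, or any event the investigator judges a substantial clinical risk. A plain Grade 3 floor would readmit them. Sections 1.2 and 1.5 already state the Grade 3 floor and can stay.

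If the sponsor intends the stricter rule, 5.2 should instead state that any irAE of any grade outside the three listed types bars re-induction. The Grade 3 wording for gastrointestinal events should then be removed from the synopsis, 5.2, 5.3 and Appendix 8, and 1.2 and 1.5 aligned.

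The choice is the sponsor's. Either version is a wording change in one amendment, with no new visit, procedure or analysis.

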### 5.3 Definition of Selected Reversible irAEs that May be Considered For Re-Treatment

Patients with selected irAEs related to ipilimumab that have completely resolved with immunosuppressive therapy or are adequately controlled with hormone therapy, may be considered for further re-treatment with ipilimumab under this study, at the time of disease progression. The list of completely reversible or medically managed immune-related adverse events (irAEs) eligible for consideration is:

- Reversible autoimmune hepatitis
- Medically managed endocrinopathy
- Reversible dermatological toxicity

All other irAEs are not considered eligible for re-treatment, including, but not limited to,

≥ Grade 3 colitis or diarrhea, or uveitis of any grade.

## 5.4 Dose Calculations

Calculate **Total Dose** as follows:

Patient body weight in kg x 3 mg = total dose in mg

Calculate **Total Infusion Volume** as follows:

Total dose in mg ÷ 5 mg/mL = infusion volume in mL

Calculate **Rate of Infusion** as follows:

Infusion volume in mL ÷ 90 minutes = rate of infusion in mL/min.

For example, a patient weighing 115 kg would be administered 345 mg of ipilimumab (115 kg x 3 mg/kg = 345 mg) with an infusion volume of 69 mL (345 mg ÷ 5 mg/mL = 69 mL). Since the final volume of the dose is less than 90 ml, add 0.9% saline to bring the final volume up to 90 ml. The infusion rate is 1.0 mL/min (90 mL ÷ 90 minutes)

## 5.5 Preparation, Administration, Dose Modification, Discontinuation

### 5.5.1 Preparation and Administration Guidelines

As with all injectable drugs, care should be taken when handling and preparing ipilimumab. Whenever possible, it should be prepared in a laminar flow hood or safety cabinet using standard precautions for the safe handling of intravenous agents, applying aseptic technique. Latex gloves are required. If ipilimumab concentrate or solution comes in contact with skin or mucosa, immediately and thoroughly wash with soap and water.

The supplies needed for ipilimumab preparation and administration include calibrated syringes and infusion containers. Ipilimumab is to be administered as an IV infusion using a volumetric pump through a 0.2 or 1.2 micrometer in-line filter (supplied by site) at the 3 mg/kg dose. See the current Investigator Brochure for additional information on allowable filter types. The infusion must be completed in 90 minutes with a 10 ml normal saline flush at the end. The ratio and rate will be specified in the pharmacy manual. The total dose must be calculated using the most recent subject weight (obtained within 3 days of the dosing visit, and prior to the infusion).

1. As ipilimumab is stored at refrigerated temperatures (2-8°C), allow the appropriate number of vials of ipilimumab to stand at room temperature for approximately five minutes.
2. Aseptically withdraw the required volume of ipilimumab solution into a syringe. Insert the needle at an angle into the ipilimumab vial by placing the needle – bevel side down – against the glass, with the tip touching the neck of the vial. The initial solution

concentration is 5 mg/mL. [Note: A sufficient excess of ipilimumab is incorporated into each vial to account for withdrawal losses].

3. Ensure that the ipilimumab solution is clear colorless, essentially free from particulate matter on visual inspection. If multiple vials are needed for a subject, it is important to use a separate sterile syringe and needle for each vial to prevent problems such as dulling of needle tip, stopper coring, repeated friction of plunger against syringe barrel wall, etc.
4. Inject ipilimumab solution withdrawn into an appropriate size evacuated infusion bag to produce a final infusion volume that has been calculated from the weight of the patient. For example, if preparing a 3 mg/kg treatment for a 65 kg patient you will use 195 mg, the drug solution volume will be 39 mL total.
5. If the total dose calculates to less than 90 mL of solution then the total dose needed should be diluted to a total volume of 90 mL in 0.9% sodium chloride.
6. Mix by GENTLY inverting several times. DO NOT shake.
7. Visually inspect the final solution. If the initial diluted solution or final dilution for infusion is not clear or contents appear to contain precipitate, the solution should be discarded.
8. Do not draw into each vial more than once. Any partial vials should be safely discarded and should not be stored for reuse.
9. Ipilimumab should be administered under the supervision of a physician experienced in the use of intravenous (IV) agents. Ipilimumab is administered as an IV infusion only.

After final drug reconciliation, unused ipilimumab solution should be disposed of at the site following procedures for the disposal of anticancer drugs.

### 5.5.2 Dose Modifications

Dose de-escalation of ipilimumab from 3 mg/kg is not allowed.

#### ***Ipilimumab Dose Skipping Rule***

Decisions to skip an ipilimumab dose must be made on specified safety criteria. Treatment with ipilimumab will be skipped or discontinued if the subject experiences at least one adverse event, specified below, considered by the investigator to be **“possibly”, “probably” or “certainly” related to ipilimumab treatment**. The investigator should contact the PI for any adverse event that will prompt a skipped dose or discontinuation of ipilimumab.

The following criteria will be used to determine dose skipping, restarting doses, or discontinuing ipilimumab.

**It may be necessary to skip study drug dosing for the following related adverse event(s):**

- Any  $\geq$  Grade 2 non-skin related adverse event (including irAEs), except for laboratory abnormalities
- Any  $\geq$  Grade 3 laboratory abnormality

- Any adverse event, laboratory abnormality or intercurrent illness that, in the judgment of the investigator, presents a substantial clinical risk to the subject with continued dosing.

**It is necessary to skip study drug dosing for the following adverse events:**

- Any  $\geq$  Grade 3 skin related adverse event regardless of causality.

**Restart ipilimumab dosing if/when the adverse event(s) resolve(s) to  $\leq$  Grade 1 severity or returns to baseline within 2 weeks of initial dose administration:**

- If the *adverse event has resolved*, restart ipilimumab dosing at the next scheduled timepoint per protocol.
- If the adverse event has not resolved in the protocol-specified dosing window (3 weeks [ $\pm 7$  days]), the next scheduled dose will be skipped and dosing will be resumed at the subsequently scheduled dose.
- If  $> 1$  dose is expected to be skipped, the dosing schedule modifications must be discussed with the coordinating investigator prior to implementation.

